## Abstract

**Background:**

Sciatica has a substantial impact on patients, and is associated with high healthcare and societal costs. Although there is variation in the clinical management of sciatica, the current model of care usually involves an initial period of ‘wait and see’ for most patients, with simple measures of advice and analgesia, followed by conservative and/or more invasive interventions if symptoms fail to resolve. A model of care is needed that does not over-treat those with a good prognosis yet identifies patients who do need more intensive treatment to help with symptoms, and return to everyday function including work. The aim of the SCOPiC trial (**SC**iatica **O**utcomes in **P**r**i**mary **C**are) is to establish whether stratified care based on subgrouping using a combination of prognostic and clinical information, with matched care pathways, is more effective than non-stratified care, for improving time to symptom resolution in patients consulting with sciatica in primary care. We will also assess the impact of stratified care on service delivery and evaluate its cost-effectiveness compared to non-stratified care.

**Methods/Design:**

Multicentre, pragmatic, parallel arm randomised trial, with internal pilot, cost-effectiveness analysis and embedded qualitative study. We will recruit 470 adult patients with sciatica from general practices in England and Wales, over 24 months. Patients will be randomised to stratified care or non-stratified care, and treated in physiotherapy and spinal specialist services, in participating NHS services. The primary outcome is time to first resolution of sciatica symptoms, measured on a 6-point ordered categorical scale, collected using text messaging. Secondary outcomes include physical function, pain intensity, quality of life, work loss, healthcare use and satisfaction with treatment, and will be collected using postal questionnaires at 4 and 12-month follow-up. Semi-structured qualitative interviews with a subsample of participants and clinicians will explore the acceptability of stratified care.

**Discussion:**

This paper presents the details of the rationale, design and processes of the SCOPiC trial. Results from this trial will contribute to the evidence base for management of patients with sciatica consulting in primary care.

**Trial registration:**

ISRCTN75449581, date: 20.11.2014.

## Background

About 60% of patients with low back pain (LBP) report pain in the leg (s) [1] although not all will be diagnosed as having sciatica. Sciatica is a common variation of LBP presenting with radiating pain in the leg and often accompanied by variable neurological changes in sensation, reflex or muscle strength in the leg [2]. The most common reason for sciatica symptoms is a disc prolapse compressing or irritating a spinal nerve root [2]. Sciatica prevalence estimates vary widely from 1.2 to 43%, a variation that is related to using different diagnostic criteria and sampling methods [3]. It is believed that many patients with sciatica have a favourable outcome and experience resolution of symptoms within 12 weeks from onset [2, 4]. However, a substantial proportion (estimated at up to 30%) continues to suffer with pain for a year or more [2]. Studies from primary and secondary care show that recovery after one year is moderate, varying from 49 to 58%, depending on the definition of recovery [5, 6]. The literature indicates that compared to LBP alone, sciatica has a more substantial impact on patients, with longer pain episodes [7], it is also responsible for a large proportion of the indirect costs and days lost from work associated with LBP. A Dutch study estimated that the cost of sciatica to society represents 13% of all LBP related costs [8], which translates to an annual impact to the UK economy of £268 million in direct medical costs and £1.9 billion in indirect costs.

The evidence for treatments for sciatica has been summarised in several systematic reviews [9–12]. Overall they highlight the poor quality of the research to date, mostly small trials limited to short**-**term follow**-**up. The results of the reviews indicate that the efficacy and tolerability of drugs commonly prescribed in primary care for sciatica (such as non**-**steroidal anti-inflammatory drugs, corticosteroids, antidepressants, anticonvulsants, muscle relaxants and opioid analgesics) is unclear [11]. There is evidence that active physiotherapy increases the proportion of sciatica patients showing improvement and is especially effective for those with severe symptoms [13, 14]. The reviews reach conflicting conclusions about the role of spinal injections, although these appear to provide pain relief in the short**-**term [15, 16]. Surgery provides more rapid recovery from the symptoms of sciatica although outcomes are similar to those from non**-**surgical care, one or two years later [4, 17]. Surgery and spinal injections are associated with more frequent and more severe adverse events [10], optimal selection criteria for eligible patients for surgery (discectomy) are lacking [18], and immediate referral to surgery for all sciatica patients is not a cost-effective model of care [10].

In practical terms, current treatments range from providing information and advice, medications, exercise, traction, acupuncture and manual therapy, to more invasive treatments such as spinal injections and surgery. Although there is variation between clinicians, generally the current model of care followed for sciatica is ‘stepped’. This typically means that initially there is a ‘wait and see’ period in primary care with advice and pain medication, then for those patients not improving after a period of weeks or months, referral to a clinician such as a physiotherapist might be considered, for treatments including exercise and manual therapy. Subsequently, patients failing to improve might be referred to specialist spinal services for investigations and further management [2]. Currently the only patients who are fast**-**tracked from primary care to spinal specialist opinion are those with suspected cauda equina syndrome or profound, widespread or progressive neurological deficit, and those who need hospitalisation due to pain severity. There are no robust estimates for the proportion of patients consulting in UK primary care with sciatica who proceed to spinal injection or spinal surgery, although some old reports estimate that between 5**-**15% of patients with sciatica proceed to disc surgery [18, 19]. Approximately 13% of patients consulting with sciatica in UK primary care are referred to spinal specialist services at some point following their initial primary care consultation [20]. Currently, there is no evidence that can robustly guide decision making about which sciatica patients to refer early for consideration of interventions such as spinal injections and/or surgery.

The UK Spinal Taskforce [21] highlighted problems in the management of sciatica and emphasised the urgent need for good quality trial evidence to underpin treatment decision-making, including better information about the clinical and cost effectiveness of early referral of patients with severe symptoms, for consideration of secondary care treatments such as surgery or spinal injections. A model of care is needed that does not over-treat those with a good prognosis, yet promptly identifies the patients who do need more active treatment to help with symptoms and return to everyday function including work [22].

A model of stratified care that uses information on the risk of persistent disabling non-specific LBP (prognostic risk: low, medium, high) and targets treatment accordingly, has been shown to be superior to non-stratified primary care [23, 24]. The approach uses a brief self-report tool - the STarT Back tool [25] which was developed for, and validated with, primary care patients with non-specific LBP (with and without leg pain). A similar model of stratified care may be beneficial for sciatica patients consulting in primary care, but evidence is lacking.

## Trial aims and objectives

The overall aim is to investigate whether the management of adult patients with sciatica presenting in primary care can be improved through a model of stratified care. The primary objective is to compare the clinical effectiveness of stratified care to non-stratified care, in terms of patient**-**reported time to resolution of sciatica symptoms.

Secondary objectives are to: a) compare the clinical effectiveness of stratified care to non**-**stratified care, on a range of important outcomes, including physical function, pain, quality of life, work loss, healthcare use and satisfaction with treatment, b) compare the cost-effectiveness of stratified care compared to non**-**stratified care, c) investigate the impact of stratified care on service delivery, specifically the proportion of patients receiving stratification-appropriate referrals and treatments, and d) determine the acceptability of aspects of the stratified care model, to patients and clinicians.

## Methods

### Design

The SCOPiC trial is a multicentre, pragmatic, assessor**-**blind, two-arm randomised controlled trial (RCT), comparing stratified care versus non-stratified care for adults with sciatica, with internal pilot and concurrent health economic evaluation and linked qualitative study.

### Setting

Participants will be recruited from approximately 30 general practices in Staffordshire, North Shropshire, Cheshire, and Wales, UK. The population in these localities is a mix of urban, inner city, semi-rural and rural. The trial involves National Health Service (NHS) general practices, NHS physiotherapy services and NHS spinal specialist services. A number of research clinics (SCOPiC sciatica clinics), in which patients are screened for eligibility and recruited to the trial, are based in primary care centres, in Staffordshire, North Shropshire (patients from general practices in Wales are seen in North Shropshire), and Cheshire.

### Participants

Participants are eligible for inclusion if they are aged 18 years and over, consulting at their general practice with back and/or leg symptoms of any duration or severity and their general practitioner (GP) (or other healthcare practitioner (HCP) in the practice) suspects sciatica, are able to communicate in English, willing to participate, able to give full written consent, have access to a mobile phone or landline, and following clinical assessment in the SCOPiC research clinic have the diagnosis of sciatica confirmed.

Exclusion criteria are: potentially serious spinal pathology (such as cauda equina syndrome, malignancy, inflammatory spondyloarthopathy), previous lumbar surgery, pregnancy, serious physical or mental co**-**morbidity preventing them from attending the research clinic and/or undergoing assessment and interventions, currently receiving ongoing care from, or have been in consultation with, a secondary care doctor or physiotherapist for the same problem in the last 3 months, are currently participating in any other sciatica research study.

### Stratified care model for sciatica

#### Stratification algorithm

We devised an algorithm to identify those sciatica patients likely to need a fast-track referral from primary care to specialist spinal services, and those who are likely to do well with treatments available in primary care. This algorithm was based on data analysis from the ATLAS study cohort [20] which provided information on the characteristics of sciatica patients most likely to be referred to spinal specialist services. Full details of the development of the stratification algorithm will be provided in a separate paper. Here we give very brief details on the stratification algorithm and the three derived subgroups. We utilised prognostic information, using the STarT Back tool [25], and clinical information based on the following clinical examination findings: interference with ability to work (including work around the house), pain below the knee, intense leg pain, and sensory changes in the painful leg during neurological examination (loss of or reduced pin prick sensation in a dermatomal distribution in the painful leg). The algorithm allocates patients to one of three subgroups, and each subgroup is matched with a care pathway. We allocated patients to **subgroup 1**, which involves referral to primary care for management options of low treatment intensity, if their total score on the STarT Back tool was less than or equal to 3 out of a possible 9. We used a combination of the STarT Back tool score and a number of findings from the clinical examination described above to direct referral to primary care management options of higher treatment intensity (**subgroup 2**), or to fast-track patients to a specialist spinal opinion and imaging tests (**subgroup 3**). The details of the care pathways for each of the three subgroups, are presented in full later in the text, under the section ‘Stratified care arm: Matched care pathways and their delivery’.

## Recruitment procedures

### Identification and invitation of potentially eligible patients

Participants are identified when they consult their GP (or other healthcare practitioner (HCP) within the practice) with symptoms of sciatica. When a patient with back and/or leg pain consults, and an appropriate Read code [26] is entered on the computer system, a ‘pop-up’ prompt screen asks the GP if he/she thinks the patient might have sciatica, and if so, to consider whether the patient is suitable to be invited to the SCOPiC sciatica clinic, taking into account trial inclusion/exclusion criteria. Entering ‘yes’ (that the patient has possible sciatica and is suitable to be invited to the SCOPiC sciatica clinic) on the computer system flags those patients thought to be suitable for invitation to the clinic and allows the GP to briefly inform the patient about the clinic and the trial. Using the same ‘pop up’ screen the GP also is asked to record what their management plan would have been for the patient outside the trial (‘continue with GP care’, ‘physiotherapy referral’, ‘specialist spinal referral’). This information will be summarised at the end of the trial in order to describe GP management preferences at first consultation (e.g. continue with GP care, refer to physiotherapy services or refer to spinal specialist services).

On a weekly basis, letters inviting patients to the SCOPiC sciatica clinic are mailed to all potentially eligible patients identified from their consultation. The letter and clinic information sheet explains that there is a research study being hosted at the SCOPiC sciatica clinic. Patients are invited to telephone the clinic administrator to make an appointment at the SCOPiC sciatica clinic. During that telephone call, the administrator carries out a brief check for suitability for the clinic. Patients who are receiving or have received care from alternative or complementary HCP practitioners such as osteopaths, chiropractors, acupuncturists or others, are not be excluded but are advised, where possible, to keep co-interventions to a minimum during the treatment phase of the trial. The administrator offers a clinic appointment within 10 working days. A letter is sent to patients to confirm their appointment details, together with a participant information sheet and a baseline questionnaire. Approximately two days before the clinic appointment, a clinic administrator telephones patients to remind them about their appointment and ask those who are interested in taking part in the research to bring their completed questionnaire.

Weekly retrospective GP practice consultation records review may also be used, if needed, as a second method of identifying potentially eligible participants. With this method there is a search for patients for whom the GP has entered one of the agreed Read codes indicating he/she suspects sciatica, so that if GPs overlook or do not have time to complete the electronic ‘pop up’ screen in the consultation, this method will ensure these patients are identified retrospectively and also invited using the same procedures described above. Duplication checks will ensure that the same patient is not invited twice.

### Full eligibility screening and informed consent

The SCOPiC sciatica clinics operate as integrated research/service clinics. Physiotherapists will explain the purpose of the clinic, and answer any questions patients have about the clinic or the trial. Patients expressing interest in participating in the trial proceed to have a standardised assessment for sciatica by the physiotherapist, to establish full eligibility and ascertain subgroup allocation. Eligibility for the trial is based on the assessing physiotherapist being ≥70% confident of a diagnosis of sciatica [27]. Patients who have leg pain thought by the assessing physiotherapist to be due to causes other than sciatica are excluded (for example: referred leg pain, hip pathology, peripheral neuropathy, vascular pain), as are patients for whom there is substantial diagnostic uncertainty. Patients included in the trial will have pain in one or both legs, plus at least one of the following self-reported symptoms or clinical findings; leg pain approximating a dermatomal distribution, leg pain worse or as bad as the back pain, leg pain made worse by coughing/sneezing/straining, subjective sensory symptoms approximating a dermatomal distribution, any degree of objective neurological findings relating to spinal nerve root (s) involvement such as sensory or reflex changes or myotomal weakness, or positive neural tension tests (straight leg raise (SLR), femoral nerve stretch). The above symptoms and signs are part of the presentation of sciatica [28, 29].

For patients who are eligible and interested in taking part in the trial, the physiotherapist explains the trial in detail, answer any questions and, if they are willing to participate, takes written informed consent. Patients who are ineligible or who do not wish to participate will receive advice and education from the physiotherapist in clinic and then continue with care as appropriate, outside the trial. Figure 1 outlines the SCOPiC recruitment procedures.

**Fig. 1 Fig1:**
[figure not shown]
Summary flow diagram of participant recruitment in the SCOPiC trial

### Randomisation and allocation concealment

Eligible patients who consent to take part are randomised to one of the two trial arms using a 1:1 web-based randomisation service through Keele Clinical Trials Unit (CTU), ensuring allocation concealment. The clinic administrator uses the web-based randomisation method (with a back-up process to telephone the CTU for randomisation in the event of web access failure), providing details of the centre (Staffordshire, North Shropshire/Wales, Cheshire) and patient subgroup allocation. Individual patients are randomised, stratified by centre and subgroup allocation, using random permuted blocks of varying size, to either stratified care or non**-**stratified care. The administrator informs the physiotherapist of the patient’s allocation (stratified care arm or control arm) and delivery of treatment will commence within the same SCOPiC clinic visit. The patient’s GP is informed in writing that the patient is participating in the trial but are not informed about which arm of the trial the patient has been randomised to. Usual clinician to clinician correspondence continues as per normal practice and the research does not interfere with this.

### Blinding and protection against bias

Selection bias at recruitment is avoided by separating the processes of determining patient eligibility and treatment allocation and by using random permuted blocks overseen by the CTU, not allowing physiotherapists assessing and treating patients to predict the next allocation in the clinic. Patients are told that the trial is comparing two primary care approaches for the treatment of sciatica, one based on matching patients to treatment using a simple tool which helps to decide on the treatment pathway most likely to help them, and one based on treatment needed as agreed by the physiotherapist in clinic and themselves. Patients randomised to non**-**stratified care are seen by physiotherapists who have not carried out their detailed clinical assessment and eligibility screen for the trial, and thus the treating physiotherapist in the control arm will remain blind both to the details of the stratification algorithm and the individual patient’s subgroup status, in order to make sure that there is no contamination between the two trial arms. It is not possible to blind physiotherapists treating participants randomised to the stratified care treatment arm, therefore, in order to further protect against contamination, no physiotherapists treating patients in the stratified care arm are involved in the treatment of any patients randomised to the control arm. Research nurses blinded to treatment allocation conduct primary outcome data collection over the telephone (for participants not using the automated text messages) and minimum data collection (secondary outcomes) over the telephone at 4 and 12-months follow-up, for patients who do not respond to questionnaires. The risk of contamination from GPs knowing to which arm a patient is randomised is very low. However, we will check whether involvement in the trial changes GPs’ referral habits for this condition by increasing GPs’ awareness about sciatica. We will check this by describing the proportion of sciatica patients referred to other services from participating general practices for the period of 12 months prior to the start of the trial and for the duration of the trial recruitment period. Using anonymised GP electronic records, we will retrospectively check referral patterns as described above. In qualitative interviews with the GPs we will also collect data on whether involvement in the trial contributed to changes in GPs’ referral decisions for patients with sciatica. The trial databases are password protected to ensure that the research nurses and trial statisticians remain blind to treatment allocation. Anonymised data comparisons between consenting and non-consenting individuals, dropouts and completers will be carried out to evaluate external validity and risk of attrition bias. Additionally, using validated outcome measures with established reliability will reduce measurement error.

### Audit of interventions

Treatment delivered in the intervention arm of the SCOPiC trial is recorded in a standardised format on Case Report Forms (CRFs). This includes, date of start and completion of treatment, number of treatments received and types of interventions (i.e. exercise, advice, manual therapy). Protocol deviations are reported and recorded. Details of the care patients receive in the ‘fast-track’ pathway and timeframe of any interventions delivered (such as surgical or injection procedures) are collected by populating CRFs with the relevant information from the clinical letters generated in the specialist clinics for each patient. Following the 12-month follow-up, reviews of hospital medical records for the patients in the ‘fast-track’ pathway for information on the sciatica treatments they have accessed will also be undertaken for completeness.

All physiotherapists who deliver care to patients in the control arm of the SCOPiC trial also record treatment details on a CRF. Similarly, this includes the dates of the start and completion of treatment, number of treatments and types of interventions received. Physiotherapy record reviews are conducted in the cases of missing or incomplete CRFs for both stratified care and control participants.

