#### Non-stratified care and its delivery

The control arm of the SCOPiC trial is based on non-stratified primary care, delivered by physiotherapists. Patients randomised to the control arm are treated by a physiotherapist in the SCOPiC sciatica clinic. For these patients, treatment includes a one**-**off session (in the same clinic visit) of advice and education. The treating physiotherapist then decides whether the patient should be discharged back to the care of their GP or be referred for community physiotherapy or to specialist spinal services. If an onward referral is required this is arranged by the physiotherapist at the clinic.

As previously mentioned, in order to avoid contamination between the stratified care arm and control arm, at the SCOPiC clinic, different physiotherapists provide treatment for patients in each of the two trial arms and the physiotherapists who are providing treatment to control care patients are unaware of the details of the stratification algorithm and individual participants’ group status.

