### Health economic outcomes

Health economic outcomes are collected to determine the costs of the interventions (stratified care and control) and other sciatica-specific healthcare utilisation. Resource use information is obtained on primary care consultations (GPs and other HCPs in the practice), secondary care consultations (e.g. hospital consultants), prescriptions, hospital based procedures (diagnostic tests, injections), nature and length of inpatient stays, surgery and over-the-counter purchases by patients. Patients are asked to distinguish between UK NHS and private provision. Cost data are collected via participant questionnaires at 4 and 12 months. If hospital records data on sciatica-related surgery or injections (to supplement patient-reported data) can be obtained, this data will be included in a sensitivity analysis. Unit costs are obtained from standard sources including the British National Formulary (BNF) [41], Unit Costs of Health and Social Care [42] and NHS Reference costs. Information is also collected from participants about their occupational status, sciatica-related time off work and reduced work performance (presenteeism) [43], to enable the calculation of productivity costs, allowing analysis from a societal cost perspective. The average wage for each respondent will be identified using UK Standard Occupational Classification coding [44] and annual earnings data for each job type [45]. The analysis will use the human capital approach, and the self-reported days of absence will be multiplied by the respondent-specific wage rate. The outcome of interest for the economic analysis is quality-adjusted life years (QALYs) and these will be calculated using EQ-5D-5L responses obtained at baseline, 4 and 12 months.

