## Qualitative study

The aim of the linked qualitative study is to understand the acceptability of the ‘fast-track’ pathway in the stratified care arm of the trial, to patients and clinicians. Qualitative research on patients’ experiences of sciatica and its management is scarce [46, 47], especially in those with most severe symptoms, and qualitative studies that report clinicians’ views of managing this condition are even less common [48]. In the SCOPiC trial stratified care arm the ‘fast-track’ pathway to spinal specialist assessment and opinion is novel, and the focus of the qualitative study is on patients in this subgroup and the clinicians involved in their management.

A purposive sample of patients randomised to the stratified care arm and who are on the ‘fast-track’ pathway will be invited for interview based on treatment centre and patient demographics including age, gender, baseline leg pain severity/disability, and also response to treatment. Interviews will be conducted after the 4 month follow-up point.

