#### Process outcomes analysis

Descriptive statistics will be used to examine healthcare resource utilisation by stratification subgroup (subgroups 1, 2, 3) and the number and percentage of participants who proceeded to secondary care treatments, and the types of interventions they received, in both trial arms – and by stratification subgroup (1, 2, 3). Non-parametric tests will be used to test for between-arm comparisons.

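### Clinic-letter and hospital-record capture of surgery and injections is specified only for the fast-track patients of the stratified arm, while secondary-care treatment is compared between arms

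*Protocol article*

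**What the plan says.** All references are to the protocol article.

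- **Audit of interventions, fast-track patients.** Details of their care, including surgical and injection procedures, "are collected by populating CRFs with the relevant information from the clinical letters generated in the specialist clinics for each patient". After the 12-month follow-up, "reviews of hospital medical records for the patients in the ‘fast-track’ pathway for information on the sciatica treatments they have accessed" are added to make the data complete.
- **Audit of interventions, control participants.** Treating physiotherapists complete a case report form. The one record review extended to both arms concerns physiotherapy: "Physiotherapy record reviews are conducted in the cases of missing or incomplete CRFs for both stratified care and control participants".
- **Who is fast-track.** Subgroup 3 under the stratified-care pathways. The Qualitative study section confirms the arm: "A purposive sample of patients randomised to the stratified care arm and who are on the ‘fast-track’ pathway".
- **Non-stratified care and its delivery.** A control patient may be "discharged back to the care of their GP or be referred for community physiotherapy or to specialist spinal services".
- **Process outcomes.** Data for each arm come from case report forms, patient questionnaires and reviews of records at participating NHS services. The type of record is not named.
- **Process outcomes analysis.** The analysis covers "the number and percentage of participants who proceeded to secondary care treatments, and the types of interventions they received, in both trial arms", also by stratification subgroup, with non-parametric tests between arms.
- **Health economic outcomes.** Costs come from participant questionnaires at 4 and 12 months. If hospital data on surgery or injections can be obtained, "this data will be included in a sensitivity analysis".

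**The concern.** A comparison of how many participants had a secondary-care treatment is fair only if such treatments are looked for equally hard in both arms. As written, the audit section searches two extra sources for a group that exists in one arm only. Its own reason for the hospital-record review, completeness, accepts that the other sources can miss events. A procedure in a control patient that goes unreported on a questionnaire has no stated second route into the data; the same procedure in a fast-track patient has two.

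If the rule is followed literally, stratified care could appear to send more patients to injections or surgery when it does not, or a real difference could be exaggerated. The report by subgroup is the most exposed, because in subgroup 3 the stratified-arm patients get the fuller search and their randomised control counterparts are not named for it. Healthcare use and the effect on service delivery are both secondary objectives.

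**Working it through.** **Step 1. Sources stated for surgery and injections**

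| Source | Stratified arm, fast-track | Control arm |
|---|---|---|
| Participant questionnaires | yes | yes |
| Specialist-clinic letters | yes | not named |
| Hospital-record review after 12 months | yes | not named |
| Physiotherapy forms and records | physiotherapy care | physiotherapy care |
| Unspecified record reviews (Process outcomes) | each arm, type not stated | each arm, type not stated |

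The audit section names both arms for physiotherapy records and fast-track patients alone for hospital records, so the asymmetry is in the stated rule.

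**Step 2. What the asymmetry could do**

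The plan has no figure of its own to reproduce. The following is an illustration.

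- p = true proportion with a procedure, set equal in both arms. I take 5–15%, the range the Background gives for disc surgery.
- s = share of procedures captured without letters or hospital records. Not given; assumed 0.6–0.9.
- f = share of stratified-arm procedures that occur in fast-track patients. Not given; assumed 0.5–0.8.
- Letters and hospital records are taken to find every fast-track procedure, and a procedure not found is counted as none.

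Observed control proportion = p × s.

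Observed stratified proportion = p × (f + (1 − f) × s).

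False ratio = (f + (1 − f) × s) / s. It does not depend on p.

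| s | f | False ratio |
|---|---|---|
| 0.9 | 0.5 | (0.5 + 0.45)/0.9 = 1.06 |
| 0.9 | 0.8 | (0.8 + 0.18)/0.9 = 1.09 |
| 0.8 | 0.5 | (0.5 + 0.40)/0.8 = 1.125 |
| 0.8 | 0.8 | (0.8 + 0.16)/0.8 = 1.20 |
| 0.6 | 0.5 | (0.5 + 0.30)/0.6 = 1.33 |
| 0.6 | 0.8 | (0.8 + 0.12)/0.6 = 1.53 |

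In counts, with 235 per arm, p = 10%, s = 0.8 and f = 0.8: 235 × 0.080 = 18.8 control participants against 235 × 0.096 = 22.6 stratified, when the truth is 23.5 in each.

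**Step 3. Effect on a test between arms**

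Using a normal-approximation test of two proportions (235 per arm, two-sided 5%), the chance of wrongly concluding that use is higher under stratified care should be 2.5%. For p = 5%, 10% and 15% it becomes:

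- s = 0.9, f = 0.5: 3–4%
- s = 0.8, f = 0.8: 6%, 9%, 12%
- s = 0.6, f = 0.8: 15%, 26%, 37%

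**Step 4. Within subgroup 3**

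Here f = 1, because all stratified-arm patients in the subgroup are allocated to fast-track. The ratio becomes 1/s: 1.11 at s = 0.9, 1.25 at 0.8 and 1.67 at 0.6.

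**Step 5. After the fix**

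With the same s in both arms, the false ratio is 1 and the upper-tail error returns to 2.5%.

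**The case against.** The strongest reply is that the Process outcomes section, not the audit section, governs the between-arm analysis. It says that data for patients in each arm come partly from record reviews at participating NHS services, and those services include the spinal specialist services. The audit section documents delivery of the trial pathways, so naming fast-track patients there need not limit other data collection. A condensed article may also leave out the detail on control records.

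Part of this stands. A reader might infer that control participants' hospital records will definitely not be reviewed; the documents do not go that far, because the Process outcomes wording leaves room for it. But that wording names no hospital records for controls, and the only record reviews spelled out are physiotherapy for both arms and hospital for fast-track. This is more than an omitted detail, since the article states a collection rule and ties it to a group found in one arm.

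A second reply is that the illustration rests on assumed inputs and counts questionnaire non-responders as having had no procedure. That is so. If non-responders leave the denominator, loss to follow-up alone does not create the gap, and only procedures missed among responders do. The sample size section's 20% dropout allowance is therefore not a measure of missed procedures.

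**Conclusion.** The concern holds in a limited form. The stated sources allow fuller ascertainment of secondary-care procedures in the stratified arm than in the control arm, and the Audit of interventions and Process outcomes sections need to be reconciled. If the extra sources only add procedures, the direction is towards higher apparent use under stratified care. The size cannot be derived from the documents: about 1.06 to 1.53 at arm level under the assumptions above, and more within subgroup 3.

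Three stronger readings are not supported:

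- **That the cost-effectiveness result is biased.** The main cost source is the same questionnaire in both arms. Hospital data enter only a sensitivity analysis, and only if obtainable. That analysis would be affected only if its records came from fast-track patients alone, which the economic section does not say.
- **That 1.25 or 1.67 applies to the whole trial.** Those ratios belong to subgroup 3 at 80% and 60% capture; at arm level they are diluted by procedures outside the fast-track. The Background's 13% is a referral rate, not a procedure rate.
- **That a stated objective asks whether stratified care raises specialist treatment.** The service-delivery objective specifies referrals and treatments appropriate to the subgroup.

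The primary outcome, self-reported time to resolution, is untouched.

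**What to change.** Choose one of two options, and align the Audit of interventions, Process outcomes and Process outcomes analysis sections with it.

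1. **Common sources.** State that every between-arm comparison of secondary-care treatment, overall and by subgroup, and any cost sensitivity analysis using hospital records, rests on sources collected in the same way in both arms. Keep the fast-track letter and hospital-record data for describing that pathway. This costs only analysis wording; the price is slightly less complete procedure counts.
2. **Common review.** If the Process outcomes wording is meant to cover hospital records in both arms, say in the audit section that the same 12-month review, with the same window and extraction rules, applies to control participants, at least those in subgroup 3. They can be listed from the randomisation stratum. Selecting controls by that baseline stratum is preferable to selecting those the clinic referred: "If an onward referral is required this is arranged by the physiotherapist at the clinic" covers clinic referrals, but a control patient discharged to the GP could reach specialist care later and be missed. This costs some added record review.

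In either case, state which records the Process outcomes section means, and whether the hospital data in the cost sensitivity analysis come from both arms.
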